### Microbiome Analysis and Bioinformatics Pipeline

Raw sequencing data will be processed in a QIIME2 (Quantitative Insights Into Microbial Ecology 2; version 2023.2; QIIME 2 Development Team) environment [25], executed within the Qiita platform (Knight Lab, University of California San Diego) [26]. Upon import into Qiita, FASTQ files will undergo automated metadata validation and quality filtering, including removal of low-quality reads, trimming of low-quality ends according to run-specific quality profiles. Adapter and primer sequences will be removed using cutadapt (version 4.2; Max Planck Institute for Developmental Biology) prior to downstream denoising. ASVs will be inferred using Deblur (Knight Lab, University of California San Diego) [27]. Deblur performs error correction and dereplication to generate high-resolution ASVs, while removing putative chimeras and low-abundance artefactual sequences as part of its standard denoising workflow. Because 16S amplicon sequencing provides only relative abundance estimates, absolute bacterial load is not quantified. This will be considered as a possible source of bias when interpreting results. Taxonomic assignment will be conducted using the pretrained Greengenes2 2024.9 full-length classifier, based on the corresponding Greengenes2 2024.9 reference taxonomy [28]. Sequences classified as chloroplast or mitochondria will be identified using Greengenes (version 13.8) and excluded [29]. Representative sequences will be generated within Qiita, and phylogenetic placement will rely on the Greengenes (version 13.8) 99% identity reference tree. Extraction blanks and PCR negative controls will be processed alongside study samples to detect potential laboratory or reagent contamination. Mock community controls were not included. Samples will be rarefied to a minimum depth of 30,000 reads for alpha diversity and beta diversity analyses. Samples below this threshold will be excluded from diversity metrics but may be retained for descriptive taxonomic summaries.

Analyses will follow a 2-level structure. First, community-level analyses where ASV-based distance matrices (Bray-Curtis, and weighted and unweighted UniFrac) will be used to assess group differences via permutational multivariate ANOVA [30]. Longitudinal microbiome changes will be evaluated by comparing within-individual distance differences across time intervals using Mann-Whitney *U* tests, visualized via principal coordinates analysis. Second, taxonomic-level analyses, in which higher-rank taxonomic profiles (phylum, genus, and species, where available) are summarized descriptively. Hypothesis testing at the taxonomic level will only be conducted if community-level differences emerge, to avoid overinterpretation of sparse compositional data. Given the modest cohort size, all analyses are designed for hypothesis-generating, exploratory interpretation.

Alpha diversity (Shannon index, observed features, and Faith phylogenetic diversity) and beta diversity (Bray-Curtis, and weighted and unweighted UniFrac) will be calculated to describe within- and between-sample diversity. Group comparisons will be analyzed using the Wilcoxon rank-sum or Kruskal-Wallis tests for alpha diversity and permutational multivariate ANOVA for beta diversity. Differential-abundance analysis will be performed using the Analysis of Composition of Microbiomes II (ANCOM-II) [31], a method developed for sparse compositional microbiome data. Given the modest sample size, differential-abundance findings will be interpreted exploratorily. All downstream analyses and visualizations will be performed in QIIME2 and a Python-based environment (Python Software Foundation). Workflow steps, parameters, and software versions will be version-controlled to ensure reproducibility. In addition to taxonomic data, analyses will integrate metadata on parity, medication use, and dietary habits. Associations between microbiome composition and clinical, lifestyle, or sociodemographic variables will be explored through correlation analyses and, where applicable, multivariate approaches such as redundancy analysis or generalized linear models.

Although DNA/RNA Shield stabilizes microbial nucleic acids, prolonged refrigerated storage before extraction may introduce subtle compositional shifts. This potential source of bias will be considered during interpretation.

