### Data Collection and Sample Handling

Sample collection was performed independently by participants at home as part of the fully remote study workflow. Final group assignment (CS vs VD) was based retrospectively on the actual mode of delivery at birth. Each participant was asked to provide 3 stool samples at predefined time points: during late pregnancy (T0, from gestational week 32 onward), within 2 to 3 days postpartum (T1), and at 90 (±10) days postpartum (T2). These time points were selected to capture baseline microbiome composition, immediate peripartum changes, and long-term recolonization dynamics. For each time point, participants received a sample collection kit that included a collection tube (DNA/RNA Shield Fecal Collection Tube, Zymo Research), a single-use stool catcher (Feces Catcher, Zymo Research), written instructions, and a prepaid return envelope. Paper-based questionnaires accompanied each sample kit and covered maternal health status, medication use, pregnancy and birth-related variables, and lifestyle factors such as nutrition and physical activity. Participants returned both the stool sample and completed questionnaire in the same shipment. Questionnaires were designed to be completed within approximately 10 minutes and spanned 2 to 3 pages, depending on the time point. Incomplete or missing forms were actively followed up by the study coordinator.

Samples were shipped by standard postal service and received by the coordinating study center. Although the exact time between sampling and mailing was not recorded for all participants, no sample exceeded the manufacturer’s recommended stability window.

Upon arrival, samples were documented and immediately stored in a temperature-monitored, alarm-secured refrigerator at 4°C to 8 °C, where they remained until DNA extraction. The median storage duration was 434 days (range: 137‐784 d), with no deviations from the defined storage conditions. Despite the stabilizing effect of DNA/RNA Shield, the wide range of storage periods may still cause subtle bias.

The nucleic acid stabilization buffer (DNA/RNA Shield) ensures preservation of microbial DNA for at least 24 months at ambient temperature (4° C‐25  °C) and indefinite stability when frozen (<−20 °C), according to the manufacturer. Accordingly, all returned samples were accepted for processing. No exclusions were made due to transport delays, damage, or temperature fluctuations.

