DNA extraction was performed using the ZymoBIOMICS 96 MagBead DNA Kit (D4308, Zymo Research) on an automated pipetting workstation (epMotion 5075t, Eppendorf). A slightly modified protocol was applied: 200 µL of fecal sample were mixed with 450 µL of lysis buffer and subjected to mechanical disruption using a bead-beating step in a TissueLyzer (30 Hz; 5 min). DNA was eluted in 50 µL of nuclease-free water and stored at 4 °C to 8  °C until library preparation. For amplification of the V3-V4 region of the 16S rRNA gene, the Quick-16S Next Generation Sequencing Library Prep Kit (D6400, Zymo Research) was used with 341f/806r primers. The protocol was modified by using half reaction volumes and performing 30 polymerase chain reaction (PCR) cycles. No fluorometric quantification was performed prior to amplification; however, postamplification quality control confirmed consistent DNA concentrations across all samples, and no samples had to be excluded due to insufficient yield or quality. Sequencing was conducted on an Illumina MiSeq platform using the MiSeq Reagent Kit v3 (600-cycle, paired-end 301 bp; MS-102‐3003, Illumina). Cluster generation occurred onboard the MiSeq instrument. Pooled libraries were denatured and diluted according to the manufacturer’s protocol and loaded at a final concentration of 12 pM. A PhiX control library (15%) was spiked in to increase run diversity and monitor sequencing quality. Quality controls included 2 extraction blanks consisting of lysis buffer from the DNA extraction kit, one of which was carried through library preparation, and 1 PCR-negative control (nuclease-free water). No spike-in standards for absolute quantification were used. A positive control from the Quick-16S Next Generation Sequencing Library Prep Kit (ZymoBIOMICS Microbial Community DNA Standard) was processed alongside study samples. Mock community controls beyond this kit-derived standard were not included. All study samples and controls were processed and sequenced in a single batch to avoid inter-batch variation.

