### Statistical Analysis Plan

The following procedures specify how the predefined outcomes will be analyzed. The analysis will follow an exploratory framework. Although simple, biologically plausible hypotheses have been specified, no formal power calculation was performed. Consequently, results will be interpreted as hypothesis-generating rather than confirmatory.

Feasibility outcomes will be summarized descriptively using proportions, medians, and ranges. Timing of sample returns relative to the predefined collection windows (T0, T1, and T2) will be evaluated by calculating time intervals (in d) between the target and actual return dates. These intervals will be summarized using medians and IQR and compared between delivery groups where appropriate. Reasons for loss to follow-up (eg, no sample returned) will be documented, and analyses will be performed on available cases without imputation of missing data. This analysis will help assess protocol adherence and identify potential logistical barriers in the home-based study model.

To address the previously defined microbiome outcomes, the following statistical approaches will be applied: group comparisons between CS and VD will be performed for each time point (T0, T1, and T2) and longitudinally within participants as well as within groups, using all available paired samples (eg, T0-T1 or T1-T2), where applicable. Alpha diversity metrics (eg, Shannon index and Chao1 richness) will be compared using nonparametric tests (Wilcoxon rank-sum or Kruskal-Wallis test). Beta diversity will be evaluated using permutational multivariate ANOVA based on distance matrices (eg, Bray-Curtis and UniFrac). Visualization will include principal coordinates analysis.

Analyses will follow a 2-level structure, with primary community-level testing and secondary, exploratory taxonomic-level summaries.

Relative abundances of microbial taxa at different taxonomic levels will be summarized descriptively.

Exploratory differential-abundance analyses will be performed using ANCOM-II, a method suitable for sparse compositional data that incorporates its own procedures for controlling false discoveries. Taxonomic-level hypothesis testing will only be performed if community-level analyses indicate meaningful group differences.

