## Results

The recruitment and sample collection phase of the study has been completed. Between May 2022 and October 2023, a total of 37 participants were enrolled, including 25 women in the CS group and 12 in the VD group. Recruitment concluded below the originally planned sample size, reflecting real-world constraints in this peripartum population. Follow-up was completed with receipt of the final stool sample in March 2024. An overview of baseline characteristics of participants who returned at least one stool sample is presented in Table 1. DNA extraction and 16S rRNA gene sequencing were completed in a single batch in October 2024. All samples passed quality control and were retained for downstream analyses. An overview of included and excluded samples by group and time point is provided in Figure 2. Bioinformatic processing and statistical analyses were initiated in June 2025 and were ongoing as of December 2025.

**Table 1. T1:** Baseline characteristics of participants who submitted at least 1 sample (N=31)^a^.

Characteristic		Total (N=31)	CS^b^ with PAP^c^ (n=20)		VD^d^ without PAP (n=11)	
Continuous variables						
Age (y), median (IQR)		37 (33-39)	37 (33-39)		36 (33-38)	
Categorical variables, n (**%**)						
Delivery mode						
CS		20 (65)	20 (100)		—^e^	
VD		11 (35)	—		11 (100)	
Multiple births						
Yes		2 (6)	2 (10)		0 (0)	
No		29 (94)	18 (90)		11 (100)	
Parity						
0		12 (39)	9 (45)		3 (27)	
1		13 (42)	5 (25)		8 (73)	
2		5 (16)	5 (25)		0 (0)	
3		0 (0)	0 (0)		0 (0)	
4		0 (0)	0 (0)		0 (0)	
5		1 (3)	1 (5)		0 (0)	
>1		19 (61)	11 (55)		8 (73)	

a Only participants in the CS group received PAP; no antibiotics were administered in the VD group.

b CS: cesarean section.

c PAP: perioperative antibiotic prophylaxis.

d VD: vaginal delivery.

e Not applicable.

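### Storage time before extraction falls from T0 to T2 within each woman, so any storage drift is mixed into the T1-T2 and T0-T2 changes, and the plan offers no analysis of it

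*Protocol article*

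**What the plan says.** Under Data Collection and Sample Handling, the article says that samples went on arrival into a refrigerator at 4 to 8 °C, "where they remained until DNA extraction". It reports that "The median storage duration was 434 days", with a range of 137 to 784 days, and grants that "the wide range of storage periods may still cause subtle bias". It cites the manufacturer that the buffer "ensures preservation of microbial DNA for at least 24 months at ambient temperature". It also says: "All study samples and controls were processed and sequenced in a single batch to avoid inter-batch variation". The Results section confirms that "DNA extraction and 16S rRNA gene sequencing were completed in a single batch in October 2024".

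The handling of storage is given under Microbiome Analysis and Bioinformatics Pipeline: "prolonged refrigerated storage before extraction may introduce subtle compositional shifts. This potential source of bias will be considered during interpretation".

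The Statistical Analysis Plan section compares the delivery groups at each time point and also "longitudinally within participants as well as within groups, using all available paired samples (eg, T0-T1 or T1-T2), where applicable". Its adjustment clause is triggered by imbalance in maternal variables. The sensitivity analyses it names are other distance metrics and other differential-abundance methods. Storage duration appears in neither list.

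**The concern.** The plan treats storage as a diffuse nuisance and single-batch processing purely as a safeguard. Yet when samples arrive in sequence and are all extracted together, the earliest is stored longest. Each within-woman change from T1 to T2 or from T0 to T2 then also compares a longer-stored sample with a shorter-stored one, always in the same direction.

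A bias of that form does not average out with more women, and judgement at the interpretation stage cannot separate it from biological change. The longitudinal half of the secondary objective is affected, in particular the T1-to-T2 step on which the hypothesis of partial resolution depends. The named sensitivity analyses would not reveal the problem, because every alternative metric or method would be run on samples with the same storage ordering.

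**Working it through.** **Inputs from the article.** T0 is from gestational week 32 onward, T1 at 2 to 3 days and T2 at 90 ± 10 days postpartum. Storage has median 434 days and range 137 to 784. The Figure 2 legend gives 31 samples at T0, 19 at T1 and 21 at T2. Last receipt was in March 2024.

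**Step 1: ordering.** Storage = extraction date − receipt date. With one extraction date, the storage difference within a woman equals the gap between her receipts.
- T1 minus T2: from 80 − 3 = 77 to 100 − 2 = 98 days; midpoint 87.5.
- T0 minus T2, assuming T0 at weeks 32 to 42 and birth by week 42 (0 to 70 days from T0 to birth): from 80 to 70 + 100 = 170 days.
- T0 minus T1, same assumption: from 2 to 70 + 3 = 73 days, so possibly only days.

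The sign is the same for every woman with paired samples received in window. A T0 sample mailed late could arrive close to T1.

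**Step 2: consistency with one extraction date.** The stated range spans 784 − 137 = 647 days. Receipts from May 2022 to March 2024 span 640 to 700 days, so one date fits. The endpoints do not fit October 2024: last receipt in March 2024 plus 137 days falls between 16 July and 15 August 2024, whereas extraction in October would make the minimum 184 to 244 days. Either extraction preceded October or the figures need reconciling. The ordering holds either way, provided extraction was one batch.

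**Step 3: what a drift would do to T1-T2.** The documents give no drift, so it is assumed, in SDs of the within-woman difference per 100 days. Spurious shift δ = drift × 87.5/100. The rejection rate is that of a two-sided 5% one-sample t-test on the differences, with noncentrality δ√n and n = 19, the most T1-T2 pairs possible.

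| Assumed drift per 100 days | δ (SD) | Rejection rate |
|---|---|---|
| 0 | 0 | 5% |
| 0.1 | 0.0875 | 6.5% |
| 0.2 | 0.175 | 11% |
| 0.3 | 0.2625 | 19% |

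For the three non-zero drifts, a 77-day gap gives about 6%, 10% and 16%; a 98-day gap gives about 7%, 13% and 23%. For T0-T1 with an assumed 30-day gap and n = 19, the rates are 5.2%, 5.7% and 6.6%, which is negligible. The t-test is only a yardstick, since the plan names rank tests and PERMANOVA.

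**Step 4: can storage be separated from time point?** Hardly within women. In an illustrative simulation (T0 receipt uniform 270 to 784 days before extraction, T0-to-birth gap uniform 0 to 56 days), time point explained about 97% of within-woman storage variance but only about 11% of total storage variance. The usable information is the between-woman spread at a fixed time point.

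For the 31 T0 samples, with an assumed storage SD of 150 days, the standard error of the slope is 1/(1.5 × √30) = 0.122 SD per 100 days. The 95% half-width is 2.045 × 0.122 = 0.25. An assumed storage SD of 100 days gives 0.37; 180 days gives 0.21.

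**The case against.** The strongest reply is that nothing in the documents shows a material drift. The buffer is stated to preserve DNA for at least 24 months, refrigeration had no recorded deviations, and the median storage is well inside that period. Drifts of 0.1 to 0.3 SD per 100 days would amount to 0.65 to 1.9 SD over the 647-day range, which sits poorly with a shift the authors call subtle. This stands: the size is unknown and zero must be in the range.

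Two of the three stated hypotheses (alpha diversity and *C. difficile* at T1) compare the delivery groups at one time point, where within-woman ordering plays no part. That also stands. So does the point that microbiome outcomes are secondary and exploratory, that the bias is disclosed twice, and that the open wording on sensitivity analyses does not exclude a storage check. But an unexcluded check is not a planned one, and neither disclosure says that the bias follows the time axis.

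Three stronger readings are tempting but not supported:
- A reader might infer that storage drift could mimic the whole perturbation-and-recovery pattern. A monotone drift moves T0, T1 and T2 one way; it cannot by itself produce departure and return. It can distort the T1-T2 step read alone.
- A reader might take 21 pairs and a 125-day T0-T2 gap and obtain 8.5%, 19% and 37%. That gap depends on T0 timing the article does not report, T0-T2 is not among its example pairs, and the drift is still assumed.
- A reader might infer from 784 days against about 730 that samples had degraded. The manufacturer's figure is a minimum, so this does not follow.

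**Conclusion.** The concern holds in a limited form. The ordering of storage by time point follows from single-batch extraction and sequential windows, for women with paired in-window samples. It matters for the within-woman and within-group T1-T2 and T0-T2 contrasts and barely for T0-T1. Comparisons of the delivery groups at one time point, and differences in change between groups with similar storage gaps, are largely protected.

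The consequence is conditional: for T1-T2, a nominal 5% test rises to about 6.5% to 19% under the assumed non-zero drifts and stays at 5% if there is none. The documents do not support saying that the longitudinal results are biased. They support saying that, as planned, those two within-group changes cannot be told apart from a storage effect, and that interpretation alone will not resolve it.

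**What to change.** In the Microbiome Analysis and Bioinformatics Pipeline and Statistical Analysis Plan sections:

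1. State that storage time is ordered by time point within women, and reconcile the 137-day minimum with the March 2024 and October 2024 dates.
2. Report storage days (extraction minus receipt date) by time point and delivery group.
3. Add a prespecified sensitivity analysis with storage days in the PERMANOVA and in an alpha-diversity regression run beside the rank tests, which take no covariate. Show results with and without the term, and report the between-woman storage slope among the T0 samples with its confidence interval.
4. Base longitudinal conclusions on the cesarean-minus-vaginal difference in change, and label within-group T1-T2 and T0-T2 changes as not separable from storage.

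The cost is small. The reported storage durations imply that the dates are on file, and the analysis was still under way in December 2025. The limits must be stated. The T0 slope is imprecise, at about ±0.25 SD per 100 days under the assumption above. If the between-woman SD equals the SD of the within-woman difference, drifts of 0.1 and 0.2 would be detected only about 12% and 36% of the time. The slope is also confounded with season and with the second centre, approved by amendment in September 2022. It therefore belongs in a sensitivity analysis and should not be a mandatory covariate in every model.

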### Outcomes

The primary outcomes of this protocol are feasibility indicators that assess the performance of the fully remote study design. These include the proportion of contacted women who enrolled; sample and questionnaire return rates at T0, T1, and T2; timeliness of sample returns relative to the predefined sampling windows; and overall participant retention across study time points. Together, these measures evaluate compliance, protocol adherence, and the suitability and scalability of the decentralized workflow for maternal microbiome research.

Microbiome-related outcomes are exploratory and focus on compositional rather than absolute changes in microbial communities, as 16S rRNA-sequencing yields relative abundances. These outcomes include alpha diversity metrics (eg, Shannon index and Chao1 richness), beta diversity metrics (eg, Bray-Curtis dissimilarity, and weighted and unweighted UniFrac distances), and relative abundances of bacterial taxa across taxonomic levels from phylum to genus with ASV-level feature tables used for technical analyses. Exploratory identification of marker taxa may be performed where feasible. No diagnostic or clinical interpretations of “dysbiosis” will be drawn.

In line with the observational design and modest, imbalanced sample size, all hypotheses are nonconfirmatory and serve to guide hypothesis-generating analyses. We hypothesize that women undergoing CS with PAP will exhibit a transient reduction in alpha diversity at T1 compared to VD; that compositional perturbations at T1 will at least partially resolve by T2; and that the relative abundance of *Clostridioides difficile* will be higher at T1 in the CS group than in VD. These hypotheses reflect biologically plausible patterns without implying confirmatory testing.

Exploratory analyses will consider associations between microbiome features and maternal metadata such as parity, medication intake, and dietary patterns, where feasible. Subgroup analyses may be limited by sample size constraints, and residual confounding is expected.

Outcomes will be described both cross-sectionally (CS vs VD at each time point) and longitudinally (across T0→T1→T2 within individuals as well as within groups). The statistical procedures for these analyses are outlined in the subsequent section.

